## 2 Methods

### 2.1 Trial Design

This is a prospective, randomized, double-blinded, placebo-controlled trial with a 1-month washout period, a 1-week run-in period, a 3-month treatment period, and a 9-month follow-up period. The participants will be arranged to enter a 1-month washout period after obtaining their informed consent during which basic treatment medications are adjusted, and then they will be allocated to enter a 1-week run-in period for lifestyle education and collection of baseline data and samples. After the run-in period, they will be randomized 1:1:1:1 to one of four groups: BBR-alone, inulin plus BBR, inulin-alone, or placebo. This study will use a stratified random method to balance the following factors: BMI ≥25 kg/m^2^ and <25 kg/m^2^, with or without chronic complications of diabetes. Measurements will be implemented at baseline prior to the intervention and at 3 months, 6 months, 9 months and 12 months from baseline. The research flowchart is shown in **Figure 1**.

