### 2.4 Outcome Assessment

#### 2.4.1 Primary and Secondary Outcomes

The primary outcome measure is the change in mean HbA1c level, measured at baseline and 3 months post-intervention, which reflects the blood glucose management status of the participants.

The secondary outcome measures include: (1) the frequency of hypoglycemic events and drug-related side effects; (2) the change in C-peptide for assessing β-cell function and the incidence of acute and chronic diabetes complications; (3) daily insulin dose and medical service utilization, such as diabetes-related hospital admissions and emergency visit rate; (4) the alteration of gut microbiota assessed by multiomics measurements and the differences in intestinal permeability; and (5) the quality of life assessed by the Audit of Diabetes Dependent Quality of Life (ADDQoL-19) containing physical functioning, symptoms, psychological well-being, social well-being, role activities and personal constructs with its Chinese version CN-ADDQoL also having the individualized properties, satisfactory reliability and validity (Cronbach’s alpha=0.941) (26).

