#### 2.4.3 Data Collection

After the screening, all qualified participants with LADA will enter a 1-month washout period. After the stable control of diabetes with insulin, all enrolled participants will complete the baseline survey for a period of 1 week. The primary endpoint results will be collected after 3 months of intervention. Then, participants will receive outpatient visits every 3 months until the end of the study. The research assistants involved in data collection and evaluation will not be informed of the grouping of participants. The evaluation and data collection process is shown in **Table 1**. The participants will record their daily dose of medications, abnormal self-monitoring of blood glucose levels, combined medications and adverse events. Before each visit, participants will be asked to fill out an online survey of nutritional status in the past week to assess calorie intake, including the content of carbohydrates, fat, protein and fiber in the diet. Nurses will instruct patients to record the type and quantity of daily food *via* online and mobile platforms. In addition, it is worth noting that participants should not consume fermented dairy products (such as yogurt) or probiotics 7 days before the visit and should avoid high-fat diets 3 days before the visit.

**Table 1 T1:** Patient flow of enrolment, intervention and outcome measurements.

		PS	M0	M3	M6	M9	M12
**Enrolment**	Recruitment	×					
	Eligibility Screening	×					
	Informed consent	×					
	Allocation		×				
**Intervention**	Insulin injection	•					•
	Experimental drugs / placebo		•	•			
**Outcomes**	Demographic characteristics (Age, sex, nationality, occupation, marital status, residence and education level)		×				
	Anthropometric variables (BMI, waist and hip circumference, heart rate and blood pressure)	•					•
	Insulin logs		•				•
	Dietary logs		•				•
	CGMS*		•				•
	Metabolic parameters (HbA1C, FBG, PBG, FCP, 2hCP, Triglyceride, Total cholesterol, HDL cholesterol, LDL cholesterol)	•					•
	HOMA-IR**		•				•
	Insulin autoantibody (GADA, IA2A, ZnT8)	×	×	×			×
	Serum inflammation markers		×	×			
	Chronic complication screening (Carotid ultrasound, UCG, fundus examination, urinary albumin-creatinine ratio, eGFR)		×				×
	Gut microbiota (Metagenomics, stool metabolomics, plasma metabolomics)		×	×			×
	Intestinal permeability		×	×			×
	Drug safety assessment (Blood routine, Liver and kidney function testing, Serum electrolytes, Blood ketones, electrocardiogram)		×	×			

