### 2.5 Data Analysis

Data analysis will be performed using SPSS 26.0 software (IBM, New York, USA). P<0.05 was regarded as statistically significant unless otherwise specified. Descriptive statistics included the mean ± standard deviation for normal distributions, median and interquartile range for otherwise, and frequency and percentage for categorical variables. Intention-to-treat analysis (ITT) will be used and multiple imputations will be handled to manage missing data. Baseline descriptive data between the control group and the intervention groups will be compared using the chi-square test for categorical variables, and ANOVA for continuous variables. The primary outcome of HbA1c will be expressed as the mean HbA1c values with standard deviations, and ANOVA will be used to compare HbA1c between groups. According to the data distribution characteristics, ANOVA or Wilcoxon rank sum test will be used to compare the changes in secondary variables within and between groups. If the difference is significant, pairwise comparisons will be performed with adjustment for multiple comparisons, and ANCOVA will be used with confounding factors such as sex and age as covariates. Spearman’s correlation analysis and partial Spearman’s correlation analysis adjusted for sex and age will be used to evaluate the relationship between changes in intestinal microbial abundance and other markers.

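### Microbiome correlations are adjusted for sex and age but not treatment arm, and the only stated threshold is an unadjusted P<0.05 (minor point on an analysis supporting a secondary outcome)

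*Protocol article*

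**What the plan says.** Section 2.5 (Data Analysis) names the method, its covariates and its purpose: Spearman and partial Spearman "correlation analysis adjusted for sex and age will be used to evaluate the relationship between changes in intestinal microbial abundance and other markers". It sets a general threshold: "P<0.05 was regarded as statistically significant unless otherwise specified". No other level is given for the correlations. Multiplicity is mentioned once, for group comparisons that follow a significant overall difference: "pairwise comparisons will be performed with adjustment for multiple comparisons".

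The measurements are broad. Table 1 in section 2.4.3 lists "Gut microbiota (Metagenomics, stool metabolomics, plasma metabolomics") at baseline, 3 months and 12 months. Section 2.4.1 makes this part of secondary outcome 4: "the alteration of gut microbiota assessed by multiomics measurements and the differences in intestinal permeability". Section 2.1 gives the design: "they will be randomized 1:1:1:1 to one of four groups: BBR-alone, inulin plus BBR, inulin-alone, or placebo".

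The article does not say whether the correlations run over all arms together or within arm. It gives no number of taxa or markers.

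**The concern.** In a randomised trial, sex and age are balanced across arms in expectation. Treatment arm is the one factor meant to move both sides of these correlations. The article says as much: the Abstract describes BBR as antidiabetic and antibacterial, and the Discussion attributes its glucose-lowering effect to action on the gut microbiota and describes inulin in similar terms. The stated adjustment set therefore leaves out the variable most likely to produce a correlation between a taxon and a metabolic marker.

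A correlation that includes between-arm variation cannot separate two cases: a taxon linked to glycaemia among patients on the same treatment, and a bystander taxon that the drug happens to shift. In addition, a screen across metagenomics and two metabolomics platforms at an unadjusted 0.05 will declare chance associations in proportion to its size. At stake is how far any reported association between taxa and markers can be trusted.

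**Working it through.** **1. The plan's own figure.** The article gives no figure for the correlation analysis. The nearest one is the sample size in section 2.1.2: difference 0.44%, SD 0.80%, two-sided alpha 0.05, power 80%, 53 evaluable per arm.
- Normal approximation: n = 2 x (1.960 + 0.842)^2 x 0.80^2 / 0.44^2 = 51.9, so 52.
- Noncentral t: power 79.3% at 52 and 80.1% at 53.

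The figure of 53 is reproduced. The standardised HbA1c effect is 0.44 / 0.80 = 0.55 SD.

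**2. Correlation induced by arm if arms are pooled.** Let a fraction p of patients respond, with within-arm SD 1, a taxon shift d, an HbA1c shift of -0.55 and no within-arm association. Then

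r = -p(1-p) x 0.55 x d / sqrt[(1 + p(1-p)d^2)(1 + p(1-p) x 0.55^2)].

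- Both BBR arms respond (p = 0.5): d = 0.55 gives -0.0756/1.0756 = -0.07; d = 1.0 gives -0.1375/sqrt(1.25 x 1.0756) = -0.12.
- Only the combination arm responds (p = 0.25): d = 0.55 gives -0.0567/1.0567 = -0.05; d = 1.0 gives -0.1031/sqrt(1.1875 x 1.0567) = -0.09.

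These are Pearson values; the simulated rank correlations agree to within about 0.005. The sign depends only on the assumed direction of the taxon shift.

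**3. How often that reaches P<0.05.** Simulation of the partial Spearman test adjusted for sex and age, 2,000 runs per scenario, no within-arm association. Each cell gives the result for 53 per arm, then 60 per arm. The taxon shifts are assumptions; the HbA1c shift is from step 1.

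| Taxon shift (SD) | Both BBR arms respond | Combination arm only |
|---|---|---|
| 0 | 5.7%, 4.7% | 5.3%, 5.5% |
| 0.3 | 8.8%, 8.9% | 6.7%, 7.0% |
| 0.55 | 16.4%, 18.0% | 10.9%, 12.6% |
| 0.8 | 29.6%, 33.2% | 19.3%, 20.6% |
| 1.0 | 39.7%, 44.4% | 25.4%, 28.2% |

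With three arm indicators added, the rate lies between 4.4% and 6.2% in every scenario. A taxon that treatment does not move stays near 5% with or without arm in the model.

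**4. Multiplicity, on either reading.** For k null correlations tested at 0.05, the expected number of false positives is 0.05k, whether or not the tests are correlated. If they are independent, the chance of at least one is 1 - 0.95^k. The article gives no k, so a range is shown.

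| k (assumed) | Expected false positives | Chance of at least one |
|---|---|---|
| 10 | 0.5 | 40% |
| 50 | 2.5 | 92% |
| 100 | 5 | 99.4% |
| 1,000 | 50 | about 100% |

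For scale, Table 1 names 13 candidate markers: nine metabolic parameters, HOMA-IR and three autoantibodies. With an assumed 20 taxa that is 260 tests and 0.05 x 260 = 13 expected false positives if all are null.

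Running the correlations separately in each arm removes the effect in steps 2 and 3 but multiplies the tests up to fourfold. At k = 100 pairs that is 400 tests and 0.05 x 400 = 20 expected false positives.

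**The case against.** The strongest reply is that pooling is stated nowhere. A reader might infer from the silence that the arms are pooled. That is the natural reading, because no arm or subgroup is named, but it remains an inference. If the correlations are run within arm, the arm-induced part of the problem disappears. This stands, and the point is worded accordingly.

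The rates are also conditional. They need treatment to shift both the taxon and the marker. The taxon shifts are assumed, and the 0.44% comes from a trial of BBR with probiotics in T2D. Insulin is titrated to glucose targets in all arms (section 2.3), which could narrow the HbA1c difference and with it the induced correlation. This stands too: treatment can create such correlations, but the document does not show that it will.

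A between-arm correlation may also be part of the signal of interest, given the proposed mechanism of BBR. It misleads only if read as an association independent of treatment. That is fair, and it is why the unadjusted correlation may still be shown descriptively.

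Finally, a condensed article may leave false discovery control to the full protocol or analysis plan, and the default threshold allows for exceptions. Silence alone would be no finding. But the article does more than stay silent: it fixes a covariate set without arm, states a threshold, and confines the stated multiplicity adjustment to pairwise group comparisons. The within-arm reading does not rescue this, because it leaves more tests at the same unadjusted level.

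**Conclusion.** The point holds as a minor one. As written, the adjustment set omits treatment arm, and 0.05 without adjustment is the only criterion stated for the correlations.

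The multiplicity part does not depend on pooling; its size depends on k, which is not given. The arm part does depend on pooling, and on the assumed taxon shifts and the 0.55 SD HbA1c shift. Under those assumptions the rejection rate rises from about 5% to between 11% and 44%, while the correlations themselves stay weak.

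A reader might go further and conclude that the trial's account of how the treatment works would rest on spurious associations. The article does not support that. It plans no mediation analysis and ties no conclusion to these correlations; its stated aim is glycaemic effectiveness, with safety and tolerability. The primary HbA1c comparison, the sample size and the group comparisons are untouched.

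**What to change.** In section 2.5, or in the full analysis plan if it does not already say so:

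- State the analysis set. Either add treatment arm to the partial Spearman covariates alongside sex and age (indicators for BBR, for inulin and for their combination, so that all four arm means are removed), or compute the correlations within arm and combine them into one estimate per pair.
- Replace P<0.05 for these analyses with Benjamini-Hochberg false discovery rate control within each omics family (metagenomics, stool metabolomics, plasma metabolomics), at a level fixed in advance, for example 5-10%.
- Label the correlations exploratory.

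This changes analysis wording only and needs no new data or patients. The price is that fewer associations will be declared, and that the arm-adjusted correlation no longer carries between-arm variation. The unadjusted correlation can be shown beside it as a description. If an existing analysis plan already contains these rules, confirming that is enough.

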## 3 Discussion

Due to the rapid rate of population aging and advances in medical technology that increase life expectancy and reduce disease mortality, the management of chronic diseases and their associated complications is a difficult issue that requires strong support from the government and society. If the treatment is poor, it will greatly reduce the quality of life of the patients and cause long-term physical and mental damage. Multiple previous studies have assessed the long-term risk of macrovascular and microvascular complications in LADA patients. In the United Kingdom Prospective Diabetes Study (UKPDS), LADA patients were found to have a lower long-term risk of major adverse cardiovascular events than patients with new-onset T2D, mainly due to their younger mean age and more favorable cardiometabolic status (27). In addition, the research team also found that in the first 9 years after diabetes diagnosis, patients with LADA had a lower risk of microvascular complications (renal failure, renal death, blindness, vitreous hemorrhage, or retinal photocoagulation), but this situation was reversed by persistently poor glycemic control thereafter, with an adjusted risk of 33% higher in patients with LADA than in T2D patients (28). Similarly, Maddaloni et al. noted that LADA patients had a lower risk of developing cardiac autonomic neuropathy than T2D patients (29). These evidences highlight the existence of an early therapeutic window in LADA to improve complication outcomes by implementing strict glycemic control.

Qianjin huanglian pill is composed of Coptis chinensis powder and fresh Rehmanniae radix, which has been a classic prescription for treating diabetes since ancient times. The hypoglycemic effect of this traditional Chinese medicine may be partly attributed to one of its main components, BBR. Clinical studies have demonstrated that BBR not only exerts a hypoglycemic effect by regulating the structure and function of the human gut microbiota, but also improves fasting and postprandial lipidemia in T2D patients to achieve better cardiovascular risk control (30, 31). Animal experiments have also shown that BBR has important potential in the treatment of diabetes-related complications such as diabetic nephropathy (32, 33), diabetic retinopathy (34, 35), diabetic cardiomyopathy (36), diabetic encephalopathy (37) and diabetic neuropathy (38) by inhibiting inflammation and oxidative stress, anti-endothelial injury, regulating glucose and lipid metabolism, inhibiting microvascular proliferation and regulating autophagy. Inulin has been reported to suppress inflammation and oxidation, modulate glucose and lipid metabolism, regulate immunity, modulate gut microbiota and improve intestinal barrier function (39, 40). Studies have shown that prebiotics can enhance the beneficial effects of BBR on glucose metabolism by modulating intestinal microbiota and their metabolites (26). Moreover, the increased Langerhans cells (LCs) in the cornea and epidermis of LADA patients with peripheral neuropathy also suggest that inflammation plays an important role in the development of diabetes-related complications (41), and the anti-inflammatory properties of BBR and inulin make them advantageous in the synergistic treatment of LADA complications. Thus, the identification of compatible ingredients to delay the progression of diabetes from natural products with metabolic regulation potential will provide effective and brand-new means for the clinical treatment of LADA and its complications. However, there remains a lack of clinical evidence in this regard in the LADA population.

Undeniably, this study has several limitations. First, the trial will be conducted only in the LADA population in China. Therefore, the results may not be directly applied to people of other races and need to be further validated by other regional or international multicenter studies in the future. Second, due to the difficulties in recruiting LADA patients, it is also not easy to maintain the balance between groups, and some participants are LADA patients who have already started drug treatment, so the results of this study may not be applicable to new-onset and mild LADA patients. In addition, the study will last for approximately one year, and the specific time of insulin use in LADA patients should be judged based on the clinical experience of the clinicians. Finally, the long-term effect of the study drugs on the gut microbial condition and complication risk of the patients is also unclear.

In conclusion, the present study will provide clinical evidence to prove the treatment effectiveness and safety of supplementation with BBR plus inulin in LADA patients. In addition, if combination medication is shown to improve blood glucose management and patient quality of life, insights gained from this study will provide new clues for future pharmacological research and clinical practices in diabetes care and glycemic control.

## Data Availability Statement

The original contributions presented in the study are included in the article/supplementary material. Further inquiries can be directed to the corresponding authors.

## Ethics Statement

The studies involving human participants were reviewed and approved by the Ethical Review Committee of Second Xiangya Hospital of Central South University (approval number: 2021–046). The patients/participants provided their written informed consent to participate in this study.

